## Abstract

**Background**: Most individuals develop smoking habits in adolescence, highlighting the need for a smoking prevention program targeted at this age group. The use of “Implementation Intentions” (If-Then plans) about how to refuse a cigarette combined with anti-smoking messages has been shown to be effective in the UK. However, there is a scarcity of data regarding school-based smoking prevention interventions among adolescents available to countries with high tobacco consumption rates, like Greece. **Objectives**: To describe the cultural adaptation procedure and the evaluation protocol for the school-based “Implementation Intentions” program aimed at reducing tobacco use susceptibility among Greek adolescents aged 13–16 in school settings. **Methods**: The present study is part of the EU-funded FRESHAIR4Life Program. We will use a mixed-methods approach with a pre- and post-intervention design in six conveniently selected secondary schools in Heraklion, Crete, Greece, to measure the intervention’s Reach, Effectiveness, Adoption, Implementation, and Maintenance using the RE-AIM framework. The study plans to involve three Master Trainers (MTs), 20–25 school teachers (to be trained by the MTs), and approximately 480 students. Participating schools will receive the “Implementation Intentions” intervention, which is based on a goal-setting technique where individuals commit to perform a particular behavior when a specific context arises. The study will consist of five sequential phases: Phase I involves training three Master Trainers (MTs) using the International Primary Care Respiratory Group (IPCRG’s) Teach-the-Teacher (TtT) curriculum, specifically focused on the implementation of our intervention. In Phase II, workshops will be held to co-create and culturally adapt the intervention. Phase III will involve teachers trained by MTs on delivering the intervention. In Phase IV, teachers will deliver the intervention among students in their schools. Data will be collected pre- and post-intervention through surveys, session logs, fidelity observations, feedback forms, and follow-up interviews or focus groups (Phase V). Quantitative data will be analyzed descriptively and by using paired t-tests and multiple linear regression analyses, while qualitative data will undergo thematic analysis. **Discussion**: The study protocol’s potential benefits extend beyond educating Greek adolescents on the risks associated with smoking. Active participation will empower and motivate young people to make informed, healthy choices. We expect the results could help create more effective, context-specific interventions, support policy changes aimed at decreasing the prevalence of adolescent smoking in Crete, Greece, and potentially be used by other countries as well.

## 1. Introduction

Tobacco use (TU) constitutes an important modifiable risk factor for Non-Communicable Diseases (NCDs), representing 70% of all mortality globally [1]. While NCDs usually emerge in adulthood, early smoking initiation during adolescence increases the probability of the development of NCDs at a younger age [2,3]. This also increases the chances of retardation of lung growth and optimal lung function, experiencing adverse respiratory symptoms such as wheezing and nighttime coughing and the risk of developing asthma during adolescence [4,5,6,7]. These short-term respiratory problems pose a risk to current quality of life and may contribute to an increased likelihood of school absenteeism from temporary illness or breathing difficulties [8]. Furthermore, the developing adolescent brain is more vulnerable to nicotine and addiction, which substantially increases the risk of greater dependence and heavier smoking later on [9]. TU during adolescence is also associated with increased risk of adverse mental health outcomes and psychiatric disorders, as well as higher prevalence of marijuana use, illicit drug use and alcohol use [10,11,12].

Adolescence is the most critical stage for tobacco consumption, as young individuals are more vulnerable to social influences, with 90% of smokers initiating before the age of 19 [13,14]. Globally, approximately 12% of adolescents aged 13–15 years old report the use of one or more types of tobacco products, and in Europe this rate reaches 12.6% [15]. A significant concern is the ongoing worldwide rise in e-cigarette and nicotine pouch use among young people, posing new public health issues and detrimental effects on adolescent well-being [16,17].

Smoking rates in Greece are higher than in other European Union countries, with a prevalence of 15% among 15–16 year olds [18]. Without effective interventions, the high rates of smoking among adolescents will escalate the public health burden, and an estimated 5.6 million of today’s youth under the age of 18 are projected to experience premature mortality from TU diseases [19].

Several primary care behavioral interventions, including education or brief counseling, have been implemented to reduce TU in low-, middle- and high-income countries that target adolescents with a primary focus on smoking cessation [20,21], yet these measures have shown limited long-term success [21,22,23,24]. However, beyond the importance of designing and implementing interventions to help smokers quit, it is crucial to work towards preventing the initiation of young people into this addiction. The focus of prevention programs should be on educating adolescents who have never smoked to increase their knowledge, develop positive attitudes towards not smoking, build self-confidence, and give them the skills to decline the use of tobacco products. Additionally, programs should prevent adolescents already experimenting with TU from continuing [25].

In this context, schools present an excellent opportunity to introduce healthy lifestyle programs, such as those aimed at preventing TU, because they have access to a large and diverse student population at a key developmental stage, at a location where these students spend much of their day. Furthermore, these settings have proven useful for facilitating changes in numerous health behaviors [26]. School-based programs, such as the INTENT program from the University of Leeds in the UK [27], use “Implementation Intentions” (specific “if…then” plans) and have shown promise in Randomized Clinical Trials by reducing smoking initiation by 6.5% among 15–16-year-olds, four years on from the start of the intervention, and 25.6% of the students in the program were less likely to report having ever smoked compared to those who did not take part [27,28,29]. By employing “Implementation Intentions”, the program supports young people in resisting tobacco products offers by increasing their motivation to abstain from smoking and then helping them develop specific personalized plans/strategies to act on that motivation, in situations where they are offered tobacco products [30,31].

Despite promising indications of school-based interventions, few rigorous evaluations exist, and systematic reviews and meta-analyses have indicated that the impact of school-based smoking programs on adolescent smoking behavior has been less significant than initially expected [32,33,34,35,36]. Nevertheless, it is important to acknowledge that current programs often demonstrate inadequate local cultural adaptation and have mainly been evaluated in high-income settings, which raises questions about their general applicability to other regions. For this reason, implementation research on the tailored, multidisciplinary NCD prevention package ‘FRESHAIR4Life: Targeting tobacco and air pollution exposure in mid to late adolescents in disadvantaged populations’, an EU-funded Horizon Europe project, was initiated to adapt and implement targeted interventions for prevention and cessation in countries with varied economies that experience high TU rates, such as Greece, Kyrgyz Republic, Pakistan, and Romania [37]. Specifically in Greece, there is a scarcity of data regarding school-based smoking prevention interventions among adolescents [38,39]. In previous research, student volunteers were tasked with developing anti-smoking audiovisual materials, which they presented and reviewed with all participating students. This approach, while significantly limiting experimental smoking among adolescents, did not affect their future smoking intentions, attitudes towards smoking, or knowledge about it [38,39]. Utilizing ancient Greek literature, myths, and poems for educational purposes in a more recent study showed potential in improving smoking-related knowledge, strengthening anti-smoking attitudes, and decreasing the likelihood of initiating or continuing smoking [38,39]. The “I do not smoke, I exercise” school program showed promising results in terms of participant knowledge, perceived control, and overall satisfaction; however, its impact on participants’ smoking behavior, students’ attitudes toward smoking, and their intention to smoke was limited [40].

The aforementioned findings have important implications for smoking prevention programs in Greece and highlight the need for further exploration of tobacco control interventions in Greek schools. Therefore, the aim of this study protocol is to describe the cultural adaptation procedure and the proposed implementation and evaluation of the school-based “Implementation Intentions” program aimed at reducing TU susceptibility among Greek adolescents aged 13–16 in school settings. The specific research questions of this study are:To what extent is the Greek adaptation of the INTENT program associated with changes in tobacco use susceptibility and related attitudes among adolescents aged 13–16?How do key stakeholders, including teachers and a representative group of adolescents, perceive the feasibility, acceptability, and potential effectiveness of the INTENT program?”

## 2. Materials and Methods

The present protocol (version 7, dated 28 February 2025) has been based on the Standard Protocol Items Recommendations for Interventional Trials (SPIRIT) (Supplementary Materials Table S1) [41].

### 2.1. Study Design

The present protocol is part of the EU-funded FRESHAIR4Life Program. This protocol outlines the five phases (Figure 1) of the adaptation, preparation, and implementation plan of a smoking prevention intervention based on “Implementation Intentions” from the INTENT project from the UK [27]. The initial phase (Phase I) will involve training three Master Trainers (MTs) using the International Primary Care Respiratory Group (IPCRG’s) Teach-the-Teacher (TtT) curriculum, specifically focused on the implementation of our intervention [42,43]. In the second phase (Phase 2), these trainers will then adapt the UK’s INTENT curriculum, employing the Actor, Action, Context, Target, Time (AACTT) framework to plan the key activities for training the school teachers [44]. Subsequently, in the third phase (Phase III), they will train school teachers from six schools in Heraklion (three middle and three high schools) to deliver (Phase IV) and assess (Phase V) the effect of the intervention on adolescents aged 13–16. It is important to acknowledge that these schools were selected in collaboration with local educational authorities, taking into consideration diversity in student populations based on socioeconomic context and school size and aligning with FRESHAIR4Life’s aims of accessibility and cultural relevance (Context-Specific Tailoring). Specifically, all six public secondary schools are situated in urban and peri-urban areas of Heraklion, Crete. The selection process, conducted in conjunction with the Directorate of Secondary Education of the Heraklion Prefecture, considered factors such as differences in school size (student enrollment) and the socioeconomic diversity of students, as indicated by neighborhood characteristics (since students enroll at the school nearest to their home). This approach also aligns with FRESHAIR4Life’s commitment to addressing the needs of disadvantaged populations. Teacher training will be offered online and in-person at the schools, and this school-centered intervention will be conducted during school hours. Outcomes will be evaluated using a mixed-methods approach (quantitative and qualitative data), guided by the RE-AIM (Reach, Effectiveness, Adoption, Implementation, Maintenance) framework, with data collection points at baseline, mid-point (between sessions), and post-implementation [45].

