### 2.2. Study Population

The participants in this study will be categorized into three groups: the MTs, the teachers and the adolescents. Firstly, a selected group of three experienced educators/trainers who will act as MTs will be recruited. These individuals will be responsible for training the school teachers and overseeing the fidelity of the intervention delivery. MTs will undergo training sessions on tobacco prevention, facilitation techniques, and the “If–Then” planning methodology. Based on their new knowledge and skills, MTs will conduct training sessions and provide feedback and support to teachers throughout the implementation phase. Secondly, school teachers will be selected to participate in the intervention. These teachers will be trained by the MTs to deliver the tobacco prevention intervention to the adolescent participants. All teachers from the participating schools (approximately n = 250) will be invited to participate in the program. However, as this is a pilot intervention, the first four to five teachers from each school will be accepted to participate in the study, resulting in a total of 20 to 25 participants. The first-come, first-served approach was primarily adopted for pragmatic reasons, aligning with the goals of a pilot implementation study. Firstly, as this is an initial feasibility and implementation protocol, the main objective is to determine if the intervention can be successfully delivered by willing teachers in a real-world setting, rather than to recruit a perfectly representative sample. Secondly, restricting participation to 4–5 teachers per school creates a practical and manageable group size for the intensive training provided. Nevertheless, and considering that each classroom includes around 20 students, we anticipate that the intervention will reach approximately 480 adolescents.

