#### 2.2.1. Selection and Preparation of Country MTs (Phase I)

Three MTs will be selected with a strong background in public health, applying facilitation techniques and addressing the diverse challenges faced by adolescents. The selected MTs will be required to be motivated and tobacco-free individuals with a proven dedication to adolescent engagement. MTs need to have completed the IPCRG’s Teach-the-Teacher (TtT) program adapted to facilitate the “Implementation Intentions” intervention. The program was conducted by IPCRG from November to December 2024 and featured interactive online sessions covering numerous topics, such as “Behaviour Change with a Focus on Adolescents”, “Teaching Skills (Learning Needs, Objectives, and Methods)”, and “The If-Then Approach and Peer Learning”. [46]. This training empowered participants to more effectively train the school teachers by transferring both the knowledge and the pedagogical techniques necessary for delivering our intervention.

Given the overlapping roles of Master Trainers in adaptation, training, and evaluation, they will document their assumptions, and roles will be clarified so that those adapting the training are not solely responsible for its evaluation. Specifically, all MTs will keep a structured adaptation logbook detailing each procedure (adaptation, training of teachers, evaluation, etc.). Moreover, MTs will focus primarily on delivery and teacher training and support, while different research team members will conduct data collection, evaluation, and analysis. Furthermore, an independent FRESHAIR4Life member will oversee all processes, receive regular updates from country team members, assess their progress, and offer feedback.

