#### 2.2.3. Selection of Students

The intervention’s target demographic is middle- and high- school students (age: 13–16 years), with the participating school teachers acting as implementers. Initially, lectures will be scheduled at all selected schools to present information on smoking prevalence, effects, and the planned intervention with headmasters, teachers, and parents invited. These lectures, presented by the MTs, will inform and clarify the intervention to participating teachers and parents, thereby encouraging parental support for student participation. Then, the headmaster or a representative teacher from each school will inform all parents/legal guardians of the adolescents about the program. The students to be included should be enrolled in the classes of the trained teachers (implementors). Each student will be given an information sheet (outlining the study), an informed consent form for their legal guardian to sign, and an assent form for them to sign. All students in the participating classes will receive the intervention, though they have the option to decline participation in its evaluation. To be eligible for the evaluation of the intervention, participants must have the ability to understand the Greek language, agree to participate in the evaluation (by signing the informed assent) and to have the consent of a parent or a guardian (by signing the informed consent). Students who do not provide signed assent and consent forms will be excluded from the evaluation and will engage in a separate activity with the headmaster (smoking prevention-related) outside the classroom during the evaluation.

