#### 2.4.1. Preparation Phase—Teaching the Volunteer Teachers (Phase III)

Teachers will participate in an intensive training program led by the selected MTs. The training will be divided into two separate structured training sessions, one held online and one face-to-face (Table 2). Both of these sessions will be delivered by the MTs, approximately one to two weeks prior to implementation. The first session (about one hour), will be held online by the MTs, who will present teachers with all the adapted and translated INTENT materials, including session guides, presentations (power point format), explanatory videos, and relevant resources, through the “Google Classroom” platform. Specifically, the MTs will introduce the program’s targets, the importance of addressing adolescent TU, and the theoretical background behind the “If–Then” implementation (e.g., “If I’m offered a cigarette, then I’ll say I don’t smoke because it affects my asthma”), while also answering questions [46]. The second session will consist of a one-hour workshop held in the school environment in each of the six participating schools (4–5 teachers in each school), where MTs will guide teachers through all the necessary techniques for a successful implementation of the intervention. The workshop will build on the foundation established in the first session, providing a hands-on experience to refine teachers’ abilities to deliver the intervention with active learning techniques. These techniques usually include open-ended questioning and active listening, practicing in pairs. Furthermore, teachers will participate in role-plays addressing common challenges of adolescents, such as peer pressure, vaping myths and truths, or students who face difficulty engaging with others. After each role-play, the group participates in a debrief, discussing what worked well and identifying areas for improvement. Each teacher will deliver a short practice segment of the intervention and will receive structured feedback from both MTs and colleagues, and will repeat the activity to refine pacing, clarity, and interaction skills, incorporating the feedback they received.

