#### 2.4.2. Implementation Phase of the Study—Teachers Utilizing the Intervention at Their Classrooms (Phase IV)

The second phase of the intervention will be based on the deliverance of the “Implementation Intentions” intervention by the teachers at the schools. The implementation, as mentioned above, will be conducted in six different schools and will consist of two structured sessions (Table 3). Both sessions, each lasting two school hours (~90 min), will be delivered by trained teachers, scheduled approximately two months apart. MTs will oversee all sessions and assist teachers where needed. In the first session, teachers will introduce our intervention to students. Introducing our intervention, teachers will explain that through this program students will have the opportunity to explore the factors in their life that may influence them to smoke. Teachers will highlight the fact that committing to do something by putting this commitment down on paper is much more likely to result in success, by creating a “Personal Plan (PP)”. This session includes interactive conversations with students addressing myths and truths about TU and the long-term effects of initiating smoking, as well as quizzes regarding TU. The first session will conclude with a written exercise outlining each student’s refusal tactics, followed by the development of their Personal Plans (PPs). The second session aims to strengthen students’ personal resilience and highlight the complexity of external influences on their decision to remain smoke-free. Moreover, teachers will examine what students can recall from the previous lecture. Students will be informed about how smoking interplays with stress and once again, they will create their PP. It should be noted that both quantitative and qualitative data will be collected by the MTs, before, during and after the intervention.

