### 2.5. Data Collection (Phase V)

Data collection for this study will be organized around the intervention. First, students and teachers will complete quantitative questionnaires. These will be given at two points, (1) before the intervention (baseline) and (2) after the two sessions (post-intervention follow-up). Second, fidelity and implementation-related data will be collected during the intervention (session logs and observational checklists). These will be collected between the two sessions. Third, qualitative data will be collected after the intervention. This will involve semi-structured interviews and focus groups with participants (students and teachers). Moreover, team-members (other than MTs) will collect the data at each phase of the intervention. As stated, both quantitative (questionnaires) and qualitative data (interviews and FGs) will be collected for this study. The questionnaires will be developed for this and will consist of closed and open questions presented in a structured format. Specifically, close-ended questions will be either Likert-type (rated 1-almost never to 5-almost always) or dichotomous (yes or no). Each question will yield a score, and these scores will be summed for a total. Higher total scores will indicate a greater level of the measured variable. The estimated time for completing both the questionnaires and the interview is approximately 60 min.

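### The protocol gives three different answers to who assesses outcomes in Phase V: arguably the delivering teachers (2.1), the Master Trainers (2.4.2), or team members other than the Master Trainers (2.2.1, 2.5)

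*Protocol article*

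**What the plan says.** Three groups are named for the work of Phase V, which section 2.5 heads as data collection.

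- **Teachers.** Section 2.1 says that the MTs will train teachers from the six schools "to deliver (Phase IV) and assess (Phase V) the effect of the intervention on adolescents". The same people are described elsewhere as deliverers only. Section 2.2 says "These teachers will be trained by the MTs to deliver the tobacco prevention intervention to the adolescent participants", and section 2.2.3 describes the student sample "with the participating school teachers acting as implementers".
- **Master Trainers.** Section 2.4.2 says that "both quantitative and qualitative data will be collected by the MTs, before, during and after the intervention". Section 2.5.3 has the MTs organize the student and teacher interviews or focus groups. Section 2.7 has the MTs analyze that material thematically.
- **Other team members.** Section 2.2.1 says that "different research team members will conduct data collection, evaluation, and analysis", in a paragraph meant to separate the MTs from evaluation. Section 2.5 says that "team-members (other than MTs) will collect the data at each phase of the intervention".

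Student outcomes come from self-administered questionnaires before the first session and after the second (section 2.5.1). They cover tobacco use and susceptibility, and at follow-up also refusal capacity and how useful the sessions seemed.

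**The concern.** The first research question asks whether the program is associated with change in susceptibility and attitudes. The evidence is what students aged 13 to 16 write about themselves at school, once before and once after the sessions. Section 3.1 acknowledges that there is no control group, so nothing in the design can absorb a shift in how candidly students answer.

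Both teachers and MTs are close to the intervention. Teachers lead the sessions in which students write their Personal Plans. MTs adapt the material, train the teachers, oversee every session and help where needed. A student who has just been through two such sessions may give the expected answer more readily to someone identified with them than to a stranger. That pull would probably be stronger at follow-up than at baseline, so it would tend to favor the program, and the paired comparison could not tell it from a real change.

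The second research question, on feasibility, acceptability and perceived effectiveness, rests largely on the interviews and focus groups. There the people who built and supported the program would also organize and interpret the feedback on it, which section 2.2.1 sets out to avoid.

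**Working it through.** No arithmetic applies. The plan states no figure on this point, and the contradiction does not depend on alpha, power, effect size or attrition. The check compares every statement on who delivers, collects, evaluates or analyzes.

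**Step 1: the clause in 2.1.** The MTs are the subject of the training. The two verbs that follow, deliver and assess, attach most naturally to the teachers being trained. Each verb carries its own phase label, and the label on the second is the one that heads section 2.5. On a literal reading, the deliverers run the data-collection phase.

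**Step 2: the teachers' role elsewhere.** Sections 2.2 and 2.2.3 give them delivery only. On the second training session, section 2.4.1 says that "MTs will guide teachers through all the necessary techniques for a successful implementation of the intervention". Neither that section nor Table 2 lists outcome assessment or questionnaire handling. Under 2.5.2 teachers answer questions about their own preparation, student engagement and the quality of Personal Plan implementation. Those are implementation data, not student tobacco outcomes. The literal reading of 2.1 therefore has no operational support.

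**Step 3: the MTs.** Section 2.4.2 covers both data types and the periods before, during and after the intervention. Section 2.5 excludes the MTs from collection at each phase. The two cannot be reconciled by assigning data types or time periods differently, because each is written to cover everything. Section 2.7 also conflicts with 2.2.1, since thematic analysis is analysis. Section 2.5.3 conflicts less sharply, because organizing an interview is not necessarily conducting it.

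**Step 4: does any passage settle it?** Section 2.5 would be the natural controlling text, but 2.4.2 contradicts it just as explicitly and nothing gives either precedence. The separation in 2.2.1 and 2.5 is also worded against the MTs and does not mention the delivering teacher. Calling the questionnaires self-administered says who fills in the form, not who hands it out, supervises or collects it. Section 2.2.3 sends students without consent outside the classroom during the evaluation. This implies that the evaluation takes place in the classroom, but who is in charge there is not stated.

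**Result.** There is one explicit contradiction (2.4.2 against 2.5 and 2.2.1), one contradiction on qualitative analysis (2.7 against 2.2.1), one weaker tension (2.5.3) and one ambiguous assignment (2.1).

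**The case against.** The strongest reply is that the sentence in 2.1 is a roadmap that packs three phases into one line and may only be stating their purpose. Every operational section makes teachers deliverers, and the absence of assessment content from their training is better evidence that they were never meant to assess. This stands: 2.1 is ambiguous, not proof of a design in which teachers evaluate their own classes.

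A reader might go further and infer that students report their tobacco use to the teacher who led the session, or that this teacher keeps their refusal plans. The documents do not support either. Students write the plans, but no passage says that a teacher takes or keeps them, and none says that a teacher hands out, reads or collects the questionnaires.

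It can also be said that 2.5 already names the collectors and that an independent FRESHAIR4Life member oversees all processes. This stands only in part. Section 2.4.2 names different collectors, and oversight does not say who does the collecting.

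Finally, details of classroom administration are commonly left to the full protocol, which is not shown. That is fair, and their absence is not the point here. The point is that the published text assigns the same task to different groups.

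**Conclusion.** Wrong as written: the article contradicts itself on who assesses outcomes. The firm part is the conflict of 2.4.2, and of 2.7 for the qualitative analysis, with 2.2.1 and 2.5. The clause in 2.1 adds a third possible assessor and should be corrected with them.

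The consequence is a risk, not a demonstrated bias. It depends on a deliverer or supporter of the sessions actually handling the questionnaires, and on students answering less candidly because of it, more so at follow-up than at baseline. The likely direction favors the program. The size is unknown. A reader might try to calculate a spurious drop in reported use by assuming that some share of users hide it, but the documents give no such share. Section 1 reports a smoking prevalence of 15% at ages 15–16 in Greece without defining it as past-30-day use, and the stated aim concerns susceptibility. Any figure so obtained would only restate the assumption.

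The correction is still worth making, because an uncontrolled pre-post comparison has no later means of removing such a bias.

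**What to change.** 1. In 2.1, delete the verb for assessment and its Phase V label from the teachers' role, and name the group that carries out Phase V.
2. In 2.4.2, replace the MTs as data collectors with the team members named in 2.5. Reconcile the interview role in 2.5.3 and the thematic analysis in 2.7 with 2.2.1 in the same way.
3. In 2.5, add a sentence that the non-MT team members already assigned hand out and collect the student questionnaires at baseline and follow-up, and that the delivering teacher neither administers nor handles them.
4. State that teachers' own ratings count only as implementation data.

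The cost for the questionnaires is wording plus minor classroom logistics at two timepoints. Section 2.5 already assigns the collectors, so no new role is created if that section is the one that holds. Moving the interviews and thematic analysis away from the MTs would shift some work to the team members whom 2.2.1 already names for evaluation and analysis.
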